#### 1.4.4 Study design

This study will be conducted in accordance with guidelines from the International Conference on Harmonization (ICH) on current Good Clinical Practice (GCP) and the ethical principles that have their origins in the Declaration of Helsinki.

In order to investigate the effects and safety of NeoRecormon in well-trained cyclists a randomized, double-blind, placebo-controlled study is most appropriate.

The total study period will be 17 weeks. Within 6 weeks prior to the start of the treatment, subjects will undergo a medical screening. A ramp exercise test on a cycle ergometer will be performed directly after the screening to familiarize with the test and to determine the subject's maximal power output. A second ramp and TTE exercise test will be performed for baseline measurements within 2 weeks prior to the first administration, but after the screening. During the 8 week treatment period subjects will be administered with NeoRecormon or placebo once a week. During the treatment period subjects will follow their usual training program and will perform a ramp exercise test (see appendix 5) every two weeks. In the 7th treatment week the subjects will also perform a TTE

exercise test (see appendix 5). After the treatment period subjects will participate in a competition (see appendix 6). A follow-up visit will be scheduled, 30 days after the last dose.

Please refer to the visit and assessment schedule for a more detailed description of the study design (see Table 1).

#### **1.4.5 Investigational drug and placebo**

Investigational drug: NeoRecormon (Active substance: Epoëtime beta)

Dosage: 2000IU, 5000IU or  $\geq 6000$  IU with a maximum of 10.000IU/week, depends on Ht percentage and Hb concentration (see Figure 1)

Administration: Subcutaneously

Placebo: Saline, 0.90% w/v NaCl.

The investigational drug and its matching placebo are indistinguishable and will be packaged in the same way. Blinding will be accomplished by using the same syringes or by covering the syringes with aluminum foil.

Eligible subjects will be randomized to one of two treatment groups on a 1:1 basis. One group will be treated with placebo and one group with NeoRecormon.

#### **1.4.6 Dosing, safety margin calculations, stopping criteria**

##### ***Dose selection and adjustments***

Please refer to Figure 1 for a detailed dosing schedule.

The review of the data and the decision on the next dose level will be made by a non-blinded CHDR staff member unconnected to the study.

##### ***Dosage Rationale***

An initial dose of 5000IU/week will be administered because previous studies showed that with this dose the above mentioned target range should be reached. If the upper limit of the target range is exceeded the dose will be interrupted until the Hb concentration falls back into the range. At that point, therapy should be restarted at 2000IU/week. If treatment weeks  $\geq 5$  and  $Hb < (1.10 \times \text{Initial Hb})$  the dose will be adjusted to  $\geq 6000$  IU/week (maximal 10.000IU/week), so that it is still possible to reach the target range within 8 weeks.

##### ***Safety margin calculations***

NeoRecormon is a marketed medication. The safety profile of this treatment is well-known (see SmPC (appendix 1) and EPAR (appendix 3)). See chapter 1.4.1 for the benefit and risk assessment.

Subcutaneously administered NeoRecormon has a half-life of 12-28h. There will be one week between subcutaneous administrations of NeoRecormon, which is sufficient time to wash-out treatment from a previous occasion.

### **Stopping criteria**

Dosing will be interrupted if

- Ht  $\geq$  52%
- Hb exceeds the upper limit of the target range (see Figure 1)
- there's an unacceptable tolerability profile based on the nature, frequency, and intensity of observed AEs

These criteria will be maintained by the non-blinded CHDR staff member unconnected to the study.

#### **1.4.7 Treatment duration**

In this study 24 subjects will be injected with NeoRecormon and 24 subjects will be injected with placebo once a week during 8 weeks.

A treatment period of 8 weeks is chosen because this will provide sufficient time to reach the target range. If the target range is not reached after 5 weeks, the dose will be adjusted. In addition, during this treatment period study objectives such as assessment of safety and efficacy can be performed adequately.

#### **1.4.8 Endpoints**

##### **Efficacy endpoints**

Efficacy will be assessed at the time points indicated in the Visit and Assessment Schedule (Table 1).

Efficacy will be assessed by:

- performance in *exercise tests*
- performance in a *competition*
- measuring markers from the haematological module of the *Athlete Biological Passport*
- measuring *blood flow*

##### *Exercise tests*

A review showed that most of the research investigating the effect of rHuEPO in cyclists focused on a parameter for maximal exercise oxygen consumption,  $V_{O_{2,max}}$ . The review showed that besides this parameter, research should also focus on parameters for sub-maximal exercise. Therefore in this study maximal as well as sub-maximal exercise parameters (see table 2) will be measured during exercise tests. Subjects will perform a ramp exercise test every two weeks during their treatment/training period and a time to exhaustion exercise test in the 7th treatment week to see if the NeoRecormon/placebo treatment has an effect on their performance. Baseline measurements for these exercise tests will be performed one week prior to the treatment period.

Before and during the exercise tests blood will be collected at predetermined stages to determine if certain protein concentrations are influenced by NeoRecormon.

Please refer to appendix 5 for more detailed descriptions of the exercise tests.

##### *Competition*

Multiple factors affect cycling performance, especially in the racing conditions seen in official competition. Therefore, in this study the effects of NeoRecormon will also be determined by performance in a competition. The competition will be designed in such a way that it closely resembles real racing conditions. During the competition certain maximal and sub-maximal exercise parameters will be measured. Before and during the competition blood will be collected at predetermined stages to determine if certain protein concentrations are influenced by

NeoRecormon. After the competition urine will be collected for a doping control and for urinalysis for a.o. proteinuria.

Please refer to appendix 6 for a more detailed description of the competition.

#### *Athlete Biological Passport*

According to the WADA, the athlete biological passport (ABP) is introduced to establish whether an athlete is manipulating his physiological variables without detecting a particular substance or method. The objective of this testing is to identify athletes in a haematological module and a steroidal module. The haematological module tests for certain markers in the body that identify the enhancement of oxygen transport. The steroidal module collects information on markers for steroid doping and aims to identify endogenous anabolic androgenic steroids. In this study only the haematological module will be conducted because rHuEPO only influences markers of this module.

In this study an ABP will be created to determine the effect of NeoRecormon on markers of the haematological module and in addition to investigate if these markers together are really able to prove that an athlete is manipulating his physiological variables. The ABP will also be administered for safety, because based on Hb concentration and Ht (two of the haematological module markers) a dose will be selected weekly (during the treatment period). Blood to measure the haematological module markers will be collected before NeoRecormon/Placebo administration and before the competition.

#### *Blood flow*

LSCI measures:

- basal blood flow
- blood flow upon occlusion-reperfusion
- Blood flow after 'exercise'

### **1.4.9 Statistical hypotheses and sample size**

#### **1.4.9.1 Power calculation based on $V_{O2,max}$**

Null hypothesis:

There's no difference between the effects of NeoRecormon and placebo on cycling performance parameters.

Based on the results of a previous study a power analysis has been performed. In this study sixteen endurance-trained men (cyclists, runners and triathletes) were assigned randomly to either the rHuEPO- (n=9) or placebo- (n=7) treated groups. Both the participants and the investigators engaged in exercise testing and blood sampling were blind with respect to the group assignment. All athletes had been in regular training for several years preceding the study and continued to train throughout the period of the study but were forbidden to participate in sport events. The load of training was not different between the rHuEPO and placebo groups throughout the 4-weeks treatment period. Moderate doses of rHuEPO or placebo were injected s.c. 3 times a week for 4 weeks in the morning. The two groups also received a daily oral dose of 200mg of iron sulphate during the 4 weeks.  $V_{O2,max}$  was evaluated before and after rHuEPO treatment by using a ramp exercise test (30W/min after a 3-min baseline of warm-up at 60W) performed to the limit of tolerance on an electrically braked cycle ergometer that controlled external power output independent of pedal cadence.

The mean  $V_{O2,max}$  before treatment was similar in rHuEPO and placebo groups ( $63.0 \pm 1.5$  vs  $64.8 \pm 2.0$  ml/min/kg).  $V_{O2,max}$  increased significantly after rHuEPO treatment in the rHuEPO group ( $68.4 \pm 1.9$  ml/min/kg) and was significantly higher than in the placebo group ( $64.6 \pm 2.0$  ml/min/kg,  $P < 0.05$ ).

Equation to determine sample size: 

$$n = 1 + 2C(s/d)^2$$

n = sample size

$\alpha$  = significance level

$1-\beta$  = the desired power of the experiment to detect the postulated effect

C = constant dependent on the value of  $\alpha$  and  $\beta$  selected (see table 4)

s = standard deviation of the variable

d = magnitude of the difference the investigator wishes to detect

**Table 4.** Constant C dependent on the value of  $\alpha$  and  $\beta$  selected. 

|           |     | $\alpha$ |       |
|-----------|-----|----------|-------|
|           |     | 0.05     | 0.01  |
| $1-\beta$ | 0.8 | 7.85     | 11.68 |
|           | 0.9 | 10.51    | 14.88 |

Factors from the previous study to calculate sample size: 

d = 68.4 (rHuEPO-group) - 64.6 (Placebo group) = 3.8 ml/min/kg

s = 1.95

$1 - \beta$  = 80%

$\alpha$  = 5%

A sample size of 6 in each group will have a power of 80% to detect a difference in means of 3.8ml/min/kg, assuming that the common standard deviations is 1.95, using a two-tailed t-test with a 0.05 two sided significance level.

A review of the available literature of the research investigating the effect of rHuEPO in cyclists showed that, after initial years of training, well-trained athletes maintain a plateau in their  $V_{O2,max}$ , but continue to improve their performance further.  This indicates that the difference between effects on  $V_{O2,max}$  between the NeoRecormon and placebo group in well-trained cyclists will be smaller. The smaller the size of the difference, the larger the sample size must be to detect a significant difference. To detect a difference of 1.5ml/min/kg with a power of 80% a sample size of 22 is needed, assuming that the common standard deviation is 1.95, using a two-tailed t-test with a 0.05 two sided significance level. When taking into account a  $\pm 10\%$  attrition rate, 24 subjects are needed in both the NeoRecormon and placebo group.

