#### 7. Subjects / Groups

A total of 48 subjects are planned to be enrolled in this study. Eligible subjects will be randomized to the NeoRecormon or Placebo treatment groups on a 1:1 basis.

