#### 1.4.9.2 Power calculation based on $P_{max}/kg$

A better endpoint would be power output per kilogram (P/kg) at a submaximal level, such as 80% of  $V_{O2,max}$ . Unfortunately no studies have been performed using this endpoint, so the effect of rHuEPO on P/kg at 80%  $V_{O2,max}$  is still unknown. The mean P/kg at 80%  $V_{O2,max}$  of 11 male professional cyclists however, is 5.2 W/kg with a standard deviation of 0.199.  Using a sample size of 22 (including 10% attrition rate) and a two-tailed t-test with a 0.05 two sided significance level a difference of 0.172 W/kg can be detected with a power of 80%. This difference would mean that a professional cyclist weighing 75 kg would go from an average of 390 W at 80%  $V_{O2,max}$  to 402.9 W. On a racing bike weighing 9 kg sitting in racing position at 25 degrees Celsius, this would produce a speed of 43.80 km/h and 44.32 km/h respectively (calculated from <http://bikecalculator.com>). In a flat terrain of 40 km this would result in a finish time of 54 min 48 sec and 54 min 09 sec, a difference of 39 seconds, which is very relevant in a race like to Tour the France.

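### The 22 per group stated for 1.5 ml/min/kg does not give 80% power with the stated two-sided test: the protocol's own formula gives 28, and 22 gives about 70%

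*Protocol*

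**What the plan says.** Section 1.4.9.1 prints a sample-size formula, n = 1 + 2C(s/d)², and in Table 4 gives C = 7.85 for α = 0.05 and 80% power. It applies this twice.

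- For the difference seen in an earlier study: "A sample size of 6 in each group will have a power of 80% to detect a difference in means of 3.8ml/min/kg".
- For a smaller difference thought more plausible in well-trained cyclists: "To detect a difference of 1.5ml/min/kg with a power of 80% a sample size of 22 is needed". The SD is again 1.95, and the sidedness of the test is explicit: "using a two-tailed t-test with a 0.05 two sided significance level".

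Allowing for attrition of about 10%, it concludes: "attrition rate, 24 subjects are needed in both the NeoRecormon and placebo group". Synopsis 8.1 repeats these figures, and Section 9.3 only refers back to Section 1.4.9. Synopsis 7 fixes the total: "A total of 48 subjects are planned to be enrolled in this study", allocated 1:1.

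Section 1.4.9.2 (also Synopsis 8.2) adds a second calculation for power output per kilogram at 80% of VO2,max, with SD 0.199. For a sample of 22 it states: "two-tailed t-test with a 0.05 two sided significance level a difference of 0.172 W/kg can be detected with a power of 80" per cent.

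**The concern.** Two neighbouring statements about a sample of 22 imply different detectable effects for the same test and power. In SD units, Section 1.4.9.1 claims 1.5/1.95 = 0.769 and Section 1.4.9.2 claims 0.172/0.199 = 0.864. With 22 analysed per group, both cannot be right.

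The doubtful figure is the one that leads to 24 per group. If it is wrong, a reader of a null VO2,max result would credit the stated test with a 20% risk of missing 1.5 ml/min/kg when the risk is nearer 30%. That matters here, because the background sections treat a lack of performance effect as an informative outcome.

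**Working it through.** **Inputs**

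- Two-sided α = 0.05, power 80%, s = 1.95 ml/min/kg, d = 3.8 and then 1.5 ml/min/kg (Section 1.4.9.1).
- C = 7.85 (Table 4).
- SD 0.199 W/kg and detectable difference 0.172 W/kg (Section 1.4.9.2).
- The 22 is per group, because the attrition step takes it to 24 in each group. Read as a total (11 per group) it would give 40% power.

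**1. The figures that reproduce**

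- d = 3.8: n = 1 + 2 × 7.85 × (1.95/3.8)² = 5.13, so 6 per group, as stated. Exact power at 6 per group is 86%.
- 0.172 W/kg: with 22 per group, the effect detectable with 80% power by a two-sided t-test is 0.8646 SD. Then 0.8646 × 0.199 = 0.172 W/kg, as stated.

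So the formula, the constant and the two-sided reading are the protocol's own.

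**2. The figure that does not**

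n = 1 + 2 × 7.85 × (1.95/1.5)² = 1 + 15.7 × 1.69 = 27.53, so 28 per group. The exact two-sided t-test gives 27.52, also 28. The stated 22 is 6 per group short.

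**3. What the planned numbers deliver** (d = 1.5, s = 1.95, two-sided 0.05, exact noncentral t)

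| n per group | Power |
|---|---|
| 22 | 70.3% |
| 24 | 74.2% |
| 28 | 80.7% |

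The difference detectable with 80% power at 22 per group is 0.8646 × 1.95 = 1.69 ml/min/kg; at 24 it is 1.61. For 22 per group to suffice for 1.5, the SD would have to be 1.5/0.8646 = 1.73.

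**4. Sample size for the stated target**

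28/0.9 = 31.1, so 32 per group (64 in total). If attrition is added as 10% on top, 28 × 1.1 = 30.8, so 31 per group (62 in total). The plan has 24 per group (48 in total).

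**5. Where 22 might come from**

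- One-sided 0.05 at 80% power: C = (1.645 + 0.842)² = 6.18, giving 21.9.
- Two-sided 0.05 at 70% power: C = 6.17, giving 21.9.

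Both round to 22 and neither is what the text states. The documents do not show which, if either, was used.

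**The case against.** The strongest reply is that VO2,max will not be analysed by the t-test in the power statement. Ramp tests are repeated every two weeks, and Section 9.9.1 plans a mixed model with baseline as covariate, keeping the unpaired t-test for parameters measured once. If 1.95 is the unadjusted SD and adjustment shrinks it by √(1 − r²), a baseline correlation r of about 0.46 restores 80% power at 22 per group, and about 0.36 at 24. The documents give no r. Assumed values of 0.3, 0.5 and 0.7 give about 74%, 82% and 94% at 22 per group. This stands to the extent that the 30% miss rate belongs to the stated test and not necessarily to the planned analysis. It does not make the printed t-test statement true.

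Three further points have some force:

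- The synopsis calls the power analysis exploratory, the primary objective is to explore, and results will carry 95% confidence intervals. That softens the consequence. The text still makes a definite power claim and derives 24 per group from it.
- The power-output calculation, on what the protocol calls a better endpoint, reproduces at 22 per group and gives separate support for a sample near that size. It does not rescue the VO2,max claim.
- Section 1.4.9.2 describes its 22 as including attrition, whereas the 22 in Section 1.4.9.1 is before attrition. The comparison between the two is therefore slightly untidy, but the error is shown by the formula alone.

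**Conclusion.** The concern holds. On the protocol's own inputs (SD 1.95, difference 1.5 ml/min/kg, two-sided 0.05, unadjusted two-group t-test), 80% power needs 28 evaluable per group, not 22. The 22 stated gives about 70% power, and the full 24 about 74%. The conclusion takes the SD of 1.95 as given and allows nothing for baseline adjustment, because the protocol assumes none in this calculation. It does not show that the planned mixed model is underpowered; that depends on a correlation the protocol does not state. A one-sided calculation is one plausible cause of the error, but the cause is not established.

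**What to change.** Keep 24 per group and correct the sentence in Section 1.4.9.1 and Synopsis 8.1, for example: *With 22 evaluable subjects per group, a two-sided 5% t-test (SD 1.95) has about 70% power for a difference of 1.5 ml/min/kg; the difference detectable with 80% power is 1.69 ml/min/kg.*

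If the sponsor wants credit for baseline adjustment, state the assumed baseline correlation and its source, and recompute. If 80% power for 1.5 ml/min/kg by the unadjusted test is a firm requirement, the sample has to rise to 31–32 per group.

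The first option changes wording only, with no effect on design, conduct or analysis. Its cost is a less favourable power statement.

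### The SD of 1.95 behind the VO2max sample size comes from ± values not labelled SD or SEM, and 22 per group does not give the stated 80% power for 1.5 ml/min/kg under either reading

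*Protocol*

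**What the plan says.** Section 1.4.9.1 takes its inputs from one earlier study, in which "sixteen endurance-trained men (cyclists, runners and triathletes) were assigned randomly to either the rHuEPO- (n=9) or placebo- (n=7) treated groups". It reports VO2max (ml/min/kg) as 63.0 ± 1.5 on rHuEPO and 64.8 ± 2.0 on placebo before treatment, and 68.4 ± 1.9 and 64.6 ± 2.0 after it. Baseline VO2max, it says, "was similar in rHuEPO and placebo groups"; after treatment the rHuEPO group is reported as significantly higher than placebo, P < 0.05. The text does not say what ± denotes, and it does not name the test.

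The section then sets d = 3.8 and s = 1.95, defines s as a standard deviation, and makes two statements:

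- "A sample size of 6 in each group will have a power of 80% to detect a difference in means of 3.8ml/min/kg".
- "To detect a difference of 1.5ml/min/kg with a power of 80% a sample size of 22 is needed", raised to 24 per group for about 10% attrition.

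Both are made "assuming that the common standard deviation is 1.95, using a two-tailed t-test with a 0.05 two sided significance level" (plural 'deviations' in the first). Synopsis section 8.1 repeats both. Section 9.9.1 plans a different analysis for repeatedly measured parameters: a mixed-model ANCOVA with baseline as covariate.

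**The concern.** One number, s = 1.95, carries both VO2max statements. An unlabelled ± in a small physiological study can be either an SD or an SEM, and with 9 and 7 subjects the two differ by a factor of about 2.6 to 3. The protocol treats the values as SDs without saying that this was checked.

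There is a second problem on the same line: even with 1.95 accepted as an SD, the step from 1.5 ml/min/kg to 22 per group does not follow from the formula and test that the section names. If the power statement stays as it is, a null VO2max result could be read as evidence against an effect of 1.5 ml/min/kg that the trial had less than the stated chance of seeing, and possibly much less.

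**Working it through.** **Inputs** (section 1.4.9.1): the four ± values above; n = 9 and 7; d = 3.8 and 1.5; s = 1.95; two-sided α = 0.05; power 80%; C = 7.85; formula n = 1 + 2C(s/d)².

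**Where 1.95 comes from.** (1.9 + 2.0)/2 = 1.95. The pooled value, √[(8 × 1.9² + 6 × 2.0²)/14], is 1.94, so the averaging itself does no harm.

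**The protocol's own figures, with 1.95 as an SD.**

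- d = 3.8: 1 + 15.7 × (1.95/3.8)² = 5.13, so 6 per group. Exact (noncentral t) power at 6 per group is 86%. This statement reproduces.
- d = 1.5: 1 + 15.7 × (1.95/1.5)² = 27.5, so 28 per group. The exact t-test also gives 28. The stated 22 does not reproduce two-sided; it is what a one-sided 5% t-test would need.
- Exact two-sided power for 1.5 is 70% at 22 per group and 74% at 24. The difference detectable with 80% power at 22 per group is 1.69 ml/min/kg.

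**If the ± values are SEMs.** SD = SEM × √n: 1.9 × √9 = 5.70 and 2.0 × √7 = 5.29. Pooled: √[(8 × 5.70² + 6 × 5.29²)/14] = 5.53.

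- Power for 1.5 at 22 per group: 14%. Detectable difference: 4.8 ml/min/kg.
- Power for 3.8 at 6 per group: 19%.

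**Baseline adjustment under the SEM reading.** Residual SD = 5.53 × √(1 − r²). The protocol gives no correlation r, so the values below are assumptions. The calculation treats a single post-baseline visit, which simplifies the repeated-measures model.

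| Assumed r | Residual SD | Power for 1.5, 22 per group | Detectable difference at 80% power |
|---|---|---|---|
| 0.7 | 3.95 | 23% | 3.4 |
| 0.8 | 3.32 | 31% | 2.9 |
| 0.9 | 2.41 | 52% | 2.1 |
| 0.95 | 1.73 | 80% | 1.5 |

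**Can the protocol's figures tell SD from SEM?** Plain unpaired t-tests on the summary data, 14 degrees of freedom:

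| Comparison | Difference | As SD | As SEM | Reported |
|---|---|---|---|---|
| Baseline | 1.8 | t = 2.06, p = 0.058 | t = 0.74, p = 0.47 | similar |
| Post-treatment | 3.8 | t = 3.88, p = 0.002 | t = 1.36, p = 0.19 | P < 0.05 |

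The baseline row sits more easily with SEMs, the post-treatment row with SDs. The second row could still fit SEMs if the source compared changes. The changes are 68.4 − 63.0 = 5.4 and 64.6 − 64.8 = −0.2, a difference of 5.6. With assumed pre-post correlations of 0.5 / 0.6 / 0.7 / 0.8, the SEM reading gives p = 0.052 / 0.033 / 0.017 / 0.005. The protocol does not say which test was used.

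**The case against.** A reader might infer that the values are in fact SEMs and that the trial has about 14% power. The documents do not support going that far. Under plain unpaired tests, the SD reading is compatible with both reported comparisons: p = 0.058 is not significant, so the groups can be called similar, and p = 0.002 agrees with P < 0.05. The SEM reading needs a change-score or repeated-measures test that the protocol does not mention.

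Nor does relative spread decide it. As SDs, the ± values are 2.4% to 3.1% of the mean, which seems narrow for a mix of cyclists, runners and triathletes. But the only comparator in the protocol is a different variable: power per kilogram at 80% of VO2max in 11 professional cyclists, which "is 5.2 W/kg with a standard deviation of 0.199", a ratio of 3.8%. That lies nearer to the SD reading than to the 7% to 8% implied by SEMs. Only the cited source can settle the question.

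Three further objections have weight. First, under the SD reading the 6-per-group sentence is correct. Second, sizing on an unadjusted SD and then adjusting for baseline is usually conservative: with 1.95 as a true SD, an assumed correlation of 0.5 gives a residual SD of 1.69 and 82% power at 22 per group. Third, the synopsis calls the power analysis exploratory, and the protocol itself says that VO2max has only a remote connection to performance.

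These limit the point but do not remove it. The sentence claims 80% for a plain two-sided t-test with s = 1.95 and 22 per group, states no baseline correlation, and on those terms is wrong.

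**Conclusion.** The point holds in a limited form. The protocol leaves open whether 1.95 is a standard deviation, and its own figures do not resolve it. Independently of that, the stated 80% power for 1.5 ml/min/kg at 22 per group is not delivered by the stated test: it is 70% under the SD reading and 14% under the SEM reading, against detectable differences of 1.69 and 4.8 ml/min/kg.

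The 70% and the 28 per group rest only on the protocol's inputs. The 14%, the 19% and the pooled 5.53 rest on the assumption that ± is an SEM. The baseline-adjusted figures of 3.4, 2.9 and 2.1 ml/min/kg rest in addition on assumed correlations of 0.7, 0.8 and 0.9. The trial's size need not change; what needs correcting is the claim attached to it.

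**What to change.** In section 1.4.9.1 and synopsis section 8.1:

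1. Check in the cited study whether ± is an SD or an SEM, and label it in the text.
2. Keep 24 per group.
3. Replace the claim of 80% power for 1.5 ml/min/kg with the power or detectable difference that 22 evaluable subjects per group give under the confirmed SD. For a plain t-test this is 70% power, or 1.69 ml/min/kg at 80% power, if SD; and 14%, or 4.8 ml/min/kg, if SEM.
4. If the figure is to reflect the baseline-adjusted model of section 9.9.1, state the baseline correlation assumed.
5. Recompute the 6-per-group sentence only if the values prove to be SEMs. If they are SDs, it can stay.

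The cost is re-reading one source and rewording two paragraphs, with no added subjects or procedures. The downside is a less favourable stated figure.
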